### Study outcomes

The primary outcome is the major perinatal morbidity rate. The composite risk of major perinatal morbidity includes: (1) In utero, intrapartum and neonatal death, defined as the fetal death in utero, during labor or prior to 28 days of age (excluding lethal congenital abnormalities); (2) APGAR score at 5 mn < 4; (3) Metabolic acidosis (umbilical arterial pH < 7 + base excess ≤ −12 mmol/l); (4) Major trauma (skull fracture, subdural/subarachnoid haemorrhage, brachial plexus injury, spinal cord injury, major genital injury, paresis/paralysis at discharge); (5) Intracerebral/intraventricular haemorrhage (grades 3 and 4); (6) Periventricular leukomalacia; (7) Seizure (occurring from delivery to discharge); (8) Invasive mechanical ventilation with endotracheal intubation; (9) Major respiratory morbidity (bronchopulmonary dysplasia treated with oxygen or ventilation at 36 weeks post menstrual age or at 28 days of life, persistent pulmonary hypertension of the newborn, pneumothorax, pulmonary haemorrhage, hyaline membrane disease requiring mechanical ventilation); (10) Necrotising enterocolitis, stage 2 and 3; 11) Hypoxic-ischemic encephalopathy (APGAR 5mn < 4 + pH < 7 + base excess < −12 mmol/L + seizure); (12) Proven neonatal sepsis/infection (positive blood or cerebrospinal fluid culture); and (13) Hypotension requiring vasopressor support. The binary primary outcome (0; 1) event is triggered by occurrence any of the above morbidities. Value 1 is attributed if at least one of the above conditions is met.

Secondary outcomes include:
*The rate of major maternal morbidity:* this indicator is measured with a composite factor of maternal morbidity including: (1) maternal death (≤ 6 weeks postpartum); (2) hysterectomy; (3) proven thromboembolic complications (thrombophlebitis, pulmonary emboli); (4) admission to intensive care unit for ≥ 4 days; (5) acute pulmonary edema/cardiogenic shock; (6) sepsis with proven bacteremia (septicemia); (7) injury/lacerations to internal organs, requiring surgical repair (bladder, bowel, large vessels); (8) symptomatic uterine rupture (complete rupture of the uterine wall with extrusion of amniotic fluid, placenta, or fetal limb outside the uterine cavity, or with rupture of the bladder, requiring surgical repair)

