*The rate of minor maternal morbidity:* this indicator is measured with a composite factor of maternal morbidity including: (1) blood transfusion; (2) postpartum hemorrhage requiring surgical procedure; (3) perineal tear of third or fourth degree; (4) cervical lacerations requiring repair; (5) dehiscence of skin wound (C-section or perineal); (6) puerperal fever (≥ 38 °C postpartum); (7) postpartum infection requiring drugs or surgery (infection of the incision (C-section or perineal), uterus (e.g. endometritis), urinary tract (≥ 10^5^ CFU/ml), respiratory tract (e.g. pneumonia)); (8) major gastrointestinal complications (intestinal occlusion); (9) obstetric anesthesia complications (neurological, cardiovascular, respiratory); (10) length of postpartum hospital stay ≥ 7 days; (11) admission to intensive care unit for less than 4 days; and (12) readmission to hospital within 40 days of childbirth
*The rate of minor perinatal morbidity:* this indicator is measured with a composite factor of perinatal morbidity including: (1) minor cardiorespiratory complications (cardiac rhythm disorders, delayed amniotic fluid clearance, transient tachypnea of the newborn); (2) non-invasive mechanical ventilation; (3) admission to the intensive care unit for less than 4 days; (4) oxygen therapy; (5) suspicion of neonatal infection (culture-negative); (6) APGAR score ≥ 4 and < 7 at 5 min; (7) acidosis (umbilical artery pH ≥ 7 and < 7.20); (8) minor trauma (lacerations, limb fracture, clavicle fracture); (9) transfusion in first 24 h; and (10) weight loss > 10% in first ten postnatal days
*Rate of trial of labour (TOL):* this is the number of women attempting a vaginal delivery divided by the total number of women with one previous C-section
*Rate of VBAC:* this is the number of vaginal deliveries divided by the total number of women with one previous cesarean delivery

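### The minor perinatal composite counts an intensive-care stay under 4 days, but no perinatal item counts a stay of 4 days or more

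*Protocol article*

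**What the plan says.** All the definitions are in the protocol article, under Study outcomes.

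- **Minor perinatal morbidity** (secondary, 10 items) includes "3) admission to the intensive care unit for less than 4 days". No other item on this list concerns intensive care or length of stay.
- **Major perinatal morbidity** (primary, 13 items) has no intensive-care or length-of-stay item. The list closes with "and (13) Hypotension requiring vasopressor support", and its scoring rule is "Value 1 is attributed if at least one of the above conditions is met".
- **Major maternal morbidity** includes "admission to intensive care unit for ≥ 4 days".
- **Minor maternal morbidity** includes "11) admission to intensive care unit for less than 4 days".

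The Hypothesis section names a lower rate of minor maternal and perinatal morbidity as the second of its secondary hypotheses. The Statistical analysis section says that secondary outcomes are handled much as the primary one is.

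**The concern.** An upper limit on a minor item makes sense when the worse range is counted elsewhere. The maternal lists do this for intensive care. Several perinatal items do it too: a 5-minute Apgar below 4 is major and 4 to below 7 is minor, invasive ventilation is major and non-invasive is minor, and trauma is divided into major and minor. For the infant's intensive-care stay, only the lower half exists.

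Two things follow for the test of the secondary hypothesis. Infants with long stays and no other listed problem disappear from both composites. And if the program moves some stays from 4 days or more to under 4, those infants change from non-event to event on the minor outcome, with no offsetting improvement recorded on the major one. A change in the opposite direction would look like a benefit.

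**Working it through.** No published figure needs reproducing, because the point rests on a definition and not on the power calculation.

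**Step 1: is anything missing from the printed lists?** The perinatal lists are numbered without a break, 1 to 13 and 1 to 10, so no item was lost in extraction. Going through all 23 items, minor item 3 is the only one that refers to an intensive-care stay.

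| Intensive-care stay | Mother | Infant |
|---|---|---|
| Under 4 days | minor, item 11 | minor, item 3 |
| 4 days or more | major, item 4 | no item |

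**Step 2: how are infants scored?** The article states the any-item rule for the primary outcome. I assume the same rule for the minor composite. Scores are (minor, major).

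| Other items met | No stay | Under 4 days | 4 days or more |
|---|---|---|---|
| None | (0,0) | (1,0) | (0,0) |
| A major item, no other minor item | (0,1) | (1,1) | (0,1) |
| Another minor item, no major item | (1,0) | (1,0) | (1,0) |
| Both | (1,1) | (1,1) | (1,1) |

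The first row is the gap: the long-stay infant scores the same as one never admitted. In the second row the infant is counted as major, but the minor score still moves the wrong way with length of stay. In the last two rows length of stay makes no difference.

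**Step 3: how large could it be?** The documents give none of these inputs, so all three are assumptions:

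- L, the share of infants staying 4 days or more: 2% to 6%
- u, the share of those with no other listed item: 5% to 40%
- s, the share of those stays shortened to under 4 days: 25%

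Uncounted infants per 1,000 = 1,000 × L × u:

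- low: 1,000 × 0.02 × 0.05 = 1
- high: 1,000 × 0.06 × 0.40 = 24

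Over the 22,080 women in the Sample size section, that is 22,080 × 0.001 ≈ 22 to 22,080 × 0.024 ≈ 530.

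False rise in the minor rate, in percentage points = 100 × L × u × s:

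- low: 100 × 0.02 × 0.05 × 0.25 = 0.025
- high: 100 × 0.06 × 0.40 × 0.25 = 0.6

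The rise counts only infants with no other item on either list. Infants in the second row of the table would add to it.

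**Step 4: what does the change do?** With item 3 reading as any admission, the last column becomes (1,0), (1,1), (1,0), (1,1). Each row is then the same for short and long stays, and the reversal is gone. The major score does not change in any cell.

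**The case against.** The strongest reply is that the practical effect may be slight. A long-stay infant is missed by both lists only if none of the other 22 items is met. Those items include oxygen therapy, non-invasive ventilation, suspected infection, a low Apgar score, acidosis, intubation and proven sepsis. This stands. It would be wrong to infer that sicker infants in general score 0.

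A second reply is that the reversal is not peculiar to this item. A mother whose stay falls below 4 days also moves from 0 to 1 on the minor maternal outcome if she has no other minor item. This is also true, when that outcome is read alone. The difference is that her long stay was counted as major, so the paired outcomes record the improvement. For the infant there is no counterpart.

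A third reply is that the program concerns choice of delivery mode, rupture risk and intrapartum care, and that records are abstracted the same way in both arms. The article gives no reason to expect a net movement of stays across the 4-day line. That limits what can be said about bias, and loss of events may be the main result. But length of stay arises after randomization, so a common definition does not cancel the effect if the program does change stays.

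A reader might also infer a second gap, in the infection items. The major list has "Proven neonatal sepsis/infection (positive blood or cerebrospinal fluid culture" and the minor list has "5) suspicion of neonatal infection (culture-negative", so an infection cultured only from another site could seem to fit neither. The text does not establish this, because culture-negative can naturally be read as negative on the blood and cerebrospinal fluid cultures that define the major item.

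Finally, an article condenses a fuller plan. Here, however, it prints complete numbered lists with a threshold. If a fuller document does count long stays, the printed definition still needs correcting.

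**Conclusion.** The gap is real and certain from the text. An infant with a stay of 4 days or more and no other listed item is a non-event on both perinatal composites, and the same infant with a shorter stay is a minor event. That loses true events and lets a shortened stay score as a new event on one secondary outcome.

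Its size cannot be determined from the documents and may be small. The ranges of 1 to 24 uncounted infants per 1,000 and 0.025 to 0.6 percentage points rest wholly on assumed inputs, and the low end is negligible.

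A reader might infer that the primary outcome is also wrong because it lacks an item for long stays. The maternal pair suggests where such an item could have gone, but nothing in the article says one was intended. The primary definition, its assumed 4.5% rate and the sample size are not called into question. The point is worth correcting because one outcome item does not do what its threshold implies, and the correction is cheap.

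**What to change.** Before any unblinded analysis, change minor perinatal item 3 to any admission to the neonatal intensive care unit, with no upper limit on length. Apply it identically to baseline and intervention-period records in both arms. Leave the 13-item primary outcome and the infection items as they are.

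The cost is one line in the outcome definition, a re-derived variable, and a check that the electronic case report form records admission whatever its length. If it does not, the source is still the medical chart, which is abstracted at least 3 months after delivery. The minor rate will be somewhat higher, and a long stay will be labelled minor, which differs from the maternal grading. The alternative of placing long stays in the major list would match that grading, but it would redefine the primary outcome and raise its rate by an amount that the documents do not allow to be estimated. The timing matters because a change made after results are seen by arm would look data-driven.

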### Randomization and allocation

In April 2017, after the 1-year baseline period, hospitals will be randomly assigned either to the intervention group or the control group. Randomization will be stratified according to level of care of each hospital (community, regional, or tertiary hospital). To avoid imbalance in the size of the two groups, we will use computer-generated, blocked randomization within each stratum, with blocks consisting of four centers or, for strata with fewer than eight hospitals, two centers. The names of participating hospitals will be coded and the randomization will be generated by an independent statistician blinded to group allocation. The Data Safety Monitoring Board will receive the results of the randomization and the key code to ensure validity of the process and reveal the distribution of both intervention and control groups to the coordination team. Local investigators at each hospital will then immediately be informed of the assignment status of their hospital.

### Data collection and management

#### Data collection

Clinical data are collected independently of the intervention. Subjects will be initially screened by the medical archives department staff in every participating hospital, and then will be validated by the data collectors according to the study inclusion and exclusion criteria. Computerized data collection will be performed on-site using Dacima Clinical Suite from Dacima Software Inc. [63] The electronic case report form includes individual clinical information about the mother and the newborn, namely maternal characteristics, prenatal care, labor and delivery and maternal and neonatal complications. In-hospital data will be abstracted by trained research nurses or medical archivists from the medical records of mothers and newborns at least 3 months after delivery; data will be abstracted in the same way at both intervention and control hospitals from April 2016 to March 2017 (baseline period) and from September 2017 to August 2019 (intervention period). Data collectors will be aware of the randomization assignments but will not be involved in outcomes assessment.

#### Data management

The Dacima Clinical Suite and the trial database are managed by the Data Management Team located at the Research Center of the CHU de Québec (Laval University, Québec City, QC) and hosted on secure servers in *Dacima software* facilities (Montreal, QC). Until the end of the trial, access to the clinical database will be restricted to the Data Management Team. All steps involved in the management of clinical data will be annually monitored by an independent Data Safety Monitoring Board (DSMB).

#### Quality control of data

Four levels of control have been set up. The first level represents the data entry controls included in the Dacima software (bounds, branching logics, associations between variables). The second level is a random case review of around 5% of all medical records by a second data collector. In addition, all cases of major perinatal and maternal morbidity will be systematically monitored for quality. The third quality control level targets specific cases of perinatal and maternal morbidity for which a consensus between the collectors and the data management team could not be reached. These cases will then be submitted to a committee of experts (obstetricians and neonatologists) for further study. Finally, the Data Management Team will assess the data completeness and quality directly in the database (fourth level of control). Discrepancies will be resolved through onsite visits and queries sent to data collectors.

### Statistical analysis plan

#### Sample size and power calculation

The sample size was calculated to maximize statistical power while minimizing the number of clusters [64]. Sample size calculations were based on a cluster RCT design [65], stratified by level of care (community, regional or tertiary care hospitals), to detect a relative reduction of 25% in major perinatal morbidity in hospitals of the intervention group compared with those of the control group. To account for clustering by hospital, we assumed an intraclass correlation coefficient of 0.001, estimated from the QUARISMA Trial data, representing 70% of deliveries in Quebec in 2010–2011 [64]. We calculated that we would have to enroll 40 hospitals in the study, with an expected total of 7360 women with one prior cesarean delivery per year (22,080 women for the 1-year baseline period and the 2-year intervention period), to achieve a power of 80% to detect a 25% relative reduction with the intervention in the major perinatal morbidity rate, assuming a baseline rate of 4.5% for the three strata, at a two-sided alpha significance level of 0.05 [64, 66].

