### Hypothesis

Our primary hypothesis is that women exposed to the PRISMA program (Process for decision-making, RISk assessment and MAnagement in obstetrics) will have a rate of major perinatal morbidity, as measured in the hospitals during the intervention period, that is reduced by 25% in comparison with the control group (relative reduction). Secondary hypotheses are that the PRISMA program will: (1) reduce the rate of major maternal morbidity, (2) reduce the rate of minor maternal and perinatal morbidity, and (3) increase the rate of VBAC.

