#### Statistical analysis

For reducing contamination bias, hospitals are the units of randomization and patients are the units of analysis [64, 67]. In the primary intention-to-treat analyses, we will assess the effect of the intervention on the rate of major perinatal morbidity using the multivariable generalized-estimating-equations extension of logistic regression, with an exchangeable covariance matrix, to account for the clustering of women within hospitals [68]. Changes in the risk of major perinatal morbidity in the two study groups between the 1-year baseline (pre-intervention) period and the 2-year intervention period will be compared with the use of an adjusted odds ratio (with 95% confidence intervals) for the interaction between group (intervention vs. control) and time period (intervention vs. baseline) [64, 65]. The adjusted odds ratio for interaction will be estimated with the use of data on women who were delivered during the baseline period or the intervention period and measures the intervention effect with the difference-in-differences approach [69, 70], which is adapted for generalized-estimating equation analyses of clustered binary outcomes [65]. In each group, the change over time, from the baseline to the intervention period, will be measured by the respective odds ratio, i.e. the exponent of the difference between log odds of cesarean delivery in intervention versus baseline periods. Then, additional change over time in the intervention group, relative to the concurrent change in the control group, will be estimated by the difference between group-specific differences. The exponent of the resulting difference-in-differences in log odds provides the adjusted odds ratio, with 95% CIs, for the interaction between group (intervention vs. control) and time (intervention vs. baseline), which will be used as the main measure of the intervention effect [64, 69, 70]. Two-tailed *P* values of less than 0.05 will be considered to indicate statistical significance.

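### The 80% power belongs to a between-arm comparison in the intervention period; the difference-in-differences odds ratio named as the main measure has about 50–56%

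*Protocol article*

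**What the plan says.** The Hypothesis section states the primary hypothesis for the morbidity outcome as a rate "as measured in the hospitals during the intervention period, that is reduced by 25% in comparison with the control group". The Sample size and power calculation section follows that framing. The trial is sized "to detect a relative reduction of 25% in major perinatal morbidity in hospitals of the intervention group compared with those of the control group", with "assuming a baseline rate of 4.5% for the three strata", and "we assumed an intraclass correlation coefficient of 0.001". It gives 40 hospitals, 7,360 women per year and 22,080 over one baseline year and two intervention years. This is said "to achieve a power of 80% to detect a 25% relative reduction with the intervention in the major perinatal morbidity rate", "at a two-sided alpha significance level of 0.05". The section mentions no interaction, no variance for the baseline rates and no between-period correlation.

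The Statistical analysis section chooses a different contrast. It fits a logistic GEE to both periods and takes the group-by-period interaction odds ratio, "which will be used as the main measure of the intervention effect". In building up that quantity it describes the change within each group as "the exponent of the difference between log odds of cesarean delivery in intervention versus baseline periods".

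**The concern.** The power statement and the primary effect measure refer to different contrasts. Comparing the arms in the intervention period involves two rates, each from 7,360 women. The interaction involves four rates, two of them from a baseline year with only 3,680 women per arm. Subtracting the baseline pays off when hospitals differ a lot and stably. At an ICC of 0.001 there is very little such variation to remove, so the subtraction mainly adds noise.

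If the interaction is the primary test, a true 25% reduction would be missed nearly half the time while the article claims an 80% chance of detecting it. A non-significant result would then be taken as stronger evidence against the programme than it is.

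**Working it through.** **Inputs.** From Sample size and power calculation: control rate 0.045; 25% reduction, so 0.03375; ICC 0.001; 7,360 women per year; two-sided alpha 0.05. From the Abstract: 20 hospitals per arm. Hence 3,680 women per arm at baseline and 7,360 per arm in the intervention period, or 184 and 368 per hospital if sizes are equal. The odds ratio is (0.03375/0.96625)/(0.045/0.955) = 0.741, so |log OR| = 0.2994.

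**1. Reproducing the stated 80% (arms compared in the intervention period).**
- With 368 women per hospital, the design effect is 1 + 367 × 0.001 = 1.367.
- SE of the risk difference = √[(0.045·0.955 + 0.03375·0.96625) × 1.367 / 7,360] = 0.00375.
- z = 0.01125/0.00375 = 3.00; power 85%.
- With 552 per hospital (22,080/40), the design effect is 1.551 and power is 80.5%.
- With 368 per hospital on average and an assumed coefficient of variation of hospital size of about 0.75, power is also 80%.

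The stated figure therefore fits this contrast.

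**2. The contrast named as the main measure (interaction log odds ratio).** Take the most favourable case, in which hospital effects are identical in both periods and cancel:

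Var = 2/(3,680·0.045·0.955) + 1/(7,360·0.045·0.955) + 1/(7,360·0.03375·0.96625)
= 0.01265 + 0.00316 + 0.00417 = 0.01997

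- SE = 0.141; z = 0.2994/0.1413 = 2.12; **power 56%**.
- The baseline cells alone supply 0.01265/0.01997 = 63% of the variance.
- Setting the ICC to zero also gives 56%.

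**3. Variants.**

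| Assumption | Log-odds scale | Risk-difference scale |
|---|---|---|
| Hospital effects cancel fully | 56% | 49% |
| Between-period correlation 0.8 (assumed) | 54% | 47% |
| Between-period correlation 0.5 (assumed) | 51% | 45% |
| Between-period correlation 0 (assumed) | 47% | 41% |

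Simulations of the interaction gave 56–60%. The top value comes from an exchangeable GEE with uncorrected robust standard errors and an assumed size variation of 0.8.

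**4. What 80% power on the interaction would take.**
- Detectable reduction with 22,080 women: 32% (log odds) or 36% (risk difference).
- Women needed for a 25% reduction with the same 1:2 period split: about 1.75 × 22,080 = 38,640 on the log-odds scale.
- Or a cut in variance to (0.2994/2.80)² = 0.0114, that is 57% of 0.01997, a fall of 43%.

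**5. What the alternative estimator gives.** Per-hospital variances, in units of p(1−p), are 0.001 + 0.999/368 = 0.00371 (intervention) and 0.001 + 0.999/184 = 0.00643 (baseline), with covariance 0.001.
- Interaction relative to intervention period alone: (0.00371 + 0.00643 − 0.002)/0.00371 = 2.19.
- Baseline-adjusted relative to intervention period alone: 1 − 0.001²/(0.00371 × 0.00643) = 0.958.
- Interaction relative to baseline-adjusted: 2.19/0.958 = 2.29.

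The baseline-adjusted comparison has about 86% power with equal hospital sizes. With an assumed size variation of 0.8 and efficient weighting, the constrained-baseline model has about 84–85%.

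**The case against.** The strongest reply is that difference-in-differences is a recognised, prespecified choice for a cluster trial with a baseline period, and that its advantage depends on the ICC. That is true. With equal hospital sizes and an ICC of 0.005, the unadjusted intervention-period comparison falls to 55%, level with the interaction at 56% when hospital effects persist fully. But 0.001 is the plan's own value, and raising the ICC does not lift the interaction to 80%. Even at 0.005 the baseline-adjusted comparison does better. Its variance is 0.00733 × 2.835 × (1 − 0.312) = 0.0143, where 0.00733 is the intervention-period binomial variance and 2.835 the design effect, so power is about 71%. The recovery of power is therefore conditional on the ICC, but the ranking is not reversed.

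A second point is that the article gives no sample-size formula. Plain inputs give 85%, so matching 80% needs 552 women per hospital or an unstated allowance for unequal sizes. That the authors powered a between-arm comparison is an inference, though one their wording supports. No reading of the printed inputs gives 80% for the interaction.

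Third, the plan works on the log-odds scale, so the 49% power and 36% detectable reduction come from a scale it does not use. On its own scale the best case is 56% and 32%. Values down to 47% need an assumed between-period correlation. Covariate adjustment is unlikely to close the gap, since a 43% cut in variance is implausible for a binary outcome at 4.5%.

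Finally, the cesarean wording has no bearing on power. The surrounding text makes the intended outcome clear, but the slip sits inside the definition of the primary effect.

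**Conclusion.** The concern holds. The 80% figure is sound for comparing arms in the intervention period and wrong for the interaction odds ratio that the article makes primary. With the plan's inputs, the interaction has 56% power for a 25% reduction if hospital effects cancel fully. It has 47–54% if they persist only partly (assumed correlation 0 to 0.8). The detectable reduction at 80% power is about 32% on the plan's scale and 36% on the risk-difference scale, not 25%. The best-case result does not depend on the ICC. What does depend on an ICC near 0.001 is how much power the alternative estimator recovers.

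**What to change.** Preferred: define the primary effect as the intervention-versus-control odds ratio in the intervention period, from the same GEE. Either adjust for each hospital's baseline morbidity rate and level of care, or use the constrained-baseline form (period and group-by-period terms, no group main effect). Randomisation within strata justifies that constraint. Keep the difference-in-differences interaction as a sensitivity analysis. With about 20 hospitals per arm, use a small-sample correction for the robust standard errors.

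Alternative: if the interaction stays primary, restate its power as about 50–56% and the detectable reduction as about 32–36%, naming the scale and the between-period correlation assumed.

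In either case, replace cesarean delivery by major perinatal morbidity in the definition of the within-group change.

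The cost is a wording change in the protocol and analysis plan, made before the analysts see outcomes by arm. No further women or data are needed, because baseline data collection is already part of the design.
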